## Abstract

**Introduction:**

The incidence of SARS-CoV-2 re-infection has not been widely evaluated in low-income and middle-income countries. Understanding immune responses elicited by SARS-CoV-2 natural infection and factors that lead to re-infection in a community setting is important for public health policy. We aim to investigate the risk of primary infection and re-infection among those without and with evidence of prior infection as defined by the presence of antibodies to SARS-CoV-2 spike protein.

**Methods and analysis:**

A baseline seroprevalence survey will test for SARS-CoV-2 antibodies among healthy adults in Vellore, India. Based on an expected seropositivity rate of 50% in the general population, with annual attack rates of 12%, 6%, 4.8% and 4% among those unvaccinated and seronegative, vaccinated and seronegative, unvaccinated and seropositive, and vaccinated and seropositive, respectively, we will recruit 1200 adults who will be followed up for a total of 24 months. Weekly self-collected saliva samples will be tested by reverse transcription-PCR (RT-PCR) to detect SARS-CoV-2 infections, for a period of 1 year. For any person testing RT-PCR positive, blood samples will be collected within 2 days of RT-PCR positivity and on days 30 and 90 to assess the kinetics and longevity of the antibody responses, B cell memory and T cell memory post-infection. The data will be analysed to estimate seroprevalence at baseline and over time, the risk factors for infection, rates of primary infection and re-infection, and provide a comparison of the rates across groups based on infection and vaccination status.

**Ethics and dissemination:**

The study has been approved by the Institutional Review Board (IRB No: 13585) of Christian Medical College and Hospital, Vellore. The results of the study will be made available through journal publications and conference presentations.

**Trial registration number:**

Central Trial Registry of India: CTRI/2020/11/029438.

Strengths and limitations of this studyThe use of saliva samples for SARS-CoV-2 surveillance will be an acceptable alternate as it is self-directed and non-invasive.Weekly salivary reverse transcription-PCR will serve as surveillance for SARS-CoV-2 at the community level in Vellore.The study involves analysis of both humoral and cellular immune responses in individuals with infections and re-infections.The immunological profile following vaccine breakthrough infections will be studied in detail.Though there is a good concordance of saliva and nasopharyngeal swab for SARS-CoV-2 surveillance, there could be some infections which may be missed with saliva sampling.

## Introduction

Immune responses to SARS-CoV-2 infection, vaccination and the immune correlates of protection are areas of active investigation.^1–4^ A few studies have shown that the development, amount and kinetics of antibodies may correlate with the clinical outcome of SARS-CoV-2 infections.^5–7^ The coordinated response between humoral and cellular immunity has been hypothesised to be protective.^8^ From a public health perspective, it is crucial to understand the duration of protective immunity offered by natural infections and vaccination. The reported duration of protection following a natural infection is around 8 months to 1 year.^2–4^ Re-infections from a different strain have been documented in persons who have recovered from a prior natural infection.^9 10^ At the population level, the incidence of re-infection over a longer term of 1–2 years due to various variants of concern (VOCs) has not been evaluated, and this is also affected by vaccination. Preliminary studies suggest that antibodies persist for 7–9 months or more post-infection.^11 12^ The rates of attrition of potential immune correlates like memory B and T cell responses, and the association of these humoral and cellular immune parameters with subsequent re-infections, particularly with VOCs, are unknown. The duration of protective immunity to SARS-CoV-2 is being measured, but so far has largely been extrapolated from the data of phylogenetically related viruses. Antibody responses to SARS-CoV-1 persist for 2–3 years^13^ and memory T cells persist for 11 years after infection.^14^ In contrast, beta coronaviruses (β-CoV) that are phylogenetically close to SARS-CoV-2 are known to re-infect humans throughout life,^15^ suggesting short-lasting protective immunity. Human-controlled infection models using common cold-associated β-CoV showed partial protection from antibodies that persist for 1 year.^16^ These findings suggest that similar protective immune mechanisms could be operative in SARS-CoV-2 as well but need detailed characterisation in populations with known viral circulation. Further, uninfected individuals could harbour antibodies and memory T cells to other β-CoV.^17^ Such cross-reactive T cell responses,^17^ targeting several epitopes on the surface proteins of SARS-CoV-2, could potentially influence the course of infection or the clinical outcomes. The limited availability of data on SARS-CoV-2 infections in low-income and middle-income countries, where exposure to other coronaviruses may differ, warrants a detailed evaluation of cross-reactive T cell and antibody landscapes in primary infections and re-infection outcomes in the community.

This protocol describes a study to estimate the incidence of infection, re-infection and vaccine breakthrough infections in a community in India. The study would also determine the antibody profile, duration of antibody persistence as well the cellular immune responses following natural COVID-19 infection and re-infection.

### Objectives and expected outcomes

The CORES Study has the objectives and outcomes as described in box 1.

Box 1Objectives and outcomes of the CORES StudyObjective 1: To estimate the seroprevalence of antibodies to SARS-CoV-2 spike protein in Vellore (May–October 2021)Outcome:The proportion of individuals ≥18 years of age who are seropositive for antibodies to spike protein of SARS-CoV-2 in Vellore.Prevalence of seropositivity across clusters (wards).Objective 2: To measure the incidence of SARS-CoV-2 infection in a cohort of individuals ≥18 years in Vellore (May 2021–October 2023)Outcome:Incidence of SARS-CoV-2 infection among those without evidence of prior infection or vaccination.Incidence of SARS-CoV-2 infection among those with evidence of prior SARS-CoV-2 infection.Incidence of SARS-CoV-2 infection in those who have received at least one dose of COVID-19 vaccine at least 14 days prior to infection.Objective 3: To track cellular and humoral immune correlates of COVID-19 infection, re-infection and clinically significant disease (May 2021–October 2023)Outcome:Kinetics and longevity of antibody responses and immunological memory.Influence of baseline memory T and B levels (both SARS-CoV-2 specific as well as cross-reactive) on infection.

## Methods and analysis

### Study setting

Vellore is a tier 2 city in northern Tamil Nadu with a population of close to 500 000. It is divided into 4 zones and 60 administrative wards. The Vellore Health and Demographic Surveillance System (VHDSS), established by the Christian Medical College (CMC), monitors a population of 120 000 people across zones 3 and 4 of the city. This study area has a very high population density predominantly belonging to the economically poorer section, and is largely homogeneous, with daily wage earners being the largest subgroup of the population.

### Study design

The study will have three components: (1) serosurvey to estimate the seroprevalence of SARS-CoV-2 spike protein antibodies in the study area; (2) prospective weekly follow-up to estimate the infection and re-infection rates in a cohort of 1200 individuals; (3) intensive follow-up of incident SARS-CoV-2 infections (both symptomatic and asymptomatic) to characterise immunological and clinical features of infection in the cohort. The study flow is in figure 1.

**Figure 1 F1:**
[figure not shown]
CORES Study flow chart. PBMC, peripheral blood mononuclear cell; RT-PCR, reverse transcription-PCR, WGS- Whole Genome Sequencing, ct- cycle threshold, Q6M- Every 6 Month.

### Study status and timeline

The cohort recruitment started on 19 May 2021 and was completed on 28 October 2021. The cohort will be followed up for a period of 2 years and data will be collected until October 2023.

### Patient and public involvement

No patients or members of the public were involved in the design or conduct of the study. We will report the data in peer-reviewed publications and share it with state health authorities. Participants will be provided with study results and interpretation at a public meeting at the end of the study.

### Inclusion and exclusion criteria

Inclusion criteria:

Age 18 years and above.Permanent residents of the selected wards.Only one member from each selected household will be enrolled.Individuals with a history of clinical illness suggestive of COVID-19 or confirmed COVID-19 in the past, who are seropositive at baseline in the serosurvey (symptomatic seropositive).Individuals seropositive at baseline, with no history of COVID-19 (asymptomatic seropositive).Individuals seronegative at baseline, stratified by the ward of residence.

Exclusion criteria:

Participant refusal of consent.Pregnant women and immunocompromised patients.Participants not willing for follow-up until the end of the study.Active cancers or bleeding disorders.

### Statistical considerations

#### Assumptions

We make the following assumptions. The assumptions were based on the early findings of the Com-CoV study as there were no published data regarding vaccine efficacy and re-infections prior to the start of the study.^18^

Fifty per cent of the population will be seropositive at baseline.Forty per cent will have received two doses of vaccine mid-way into the study.The annual incidence of SARS-CoV-2 infection detected by the salivary PCR in those unvaccinated and have no detectable antibodies (unexposed) at baseline will be 12%.The annual incidence of SARS-CoV-2 infection detected by the salivary PCR in those vaccinated and unexposed at baseline will be 6% (Vaccine Effectiveness (VE) 50% against infection).The annual incidence of SARS-CoV-2 infection detected by the salivary PCR in those unvaccinated and who have antibodies (exposed) at baseline will be 4.8%.The annual incidence of SARS-CoV-2 infection detected by the salivary PCR in those vaccinated and exposed at baseline will be 4%.

Based on these assumptions, for 90% power to detect a 5% difference in the rate of re-infection and primary infection in the cohort, a sample size of 1200 participants is proposed, after allowing for a 10% dropout rate.

## Key definitions

Seropositive is defined as serum/plasma samples positive for IgG spike protein antibody to SARS-CoV-2 identified by LIAISON SARS-CoV-2 TrimericS IgG assay by Diasorin platform. The cut-off for seropositivity is more than or equal to 33.8 BAU/mL.Past asymptomatic infection refers to those who are seropositive (or documented reverse transcription-PCR (RT-PCR) positive >1 month in the past) but are neither antigen or RT-PCR positive at baseline assessment AND have had no symptoms of COVID-19.Recent asymptomatic infection refers to those who are seronegative AND are either RT-PCR or antigen positive AND have had no symptoms of COVID-19.Past symptomatic infection refers to those who are seropositive (or documented RT-PCR positive >1 month in the past) but are neither antigen or RT-PCR positive at assessment AND have had symptoms of COVID-19 in the past.Recent symptomatic infection refers to those who are seronegative AND are either RT-PCR or antigen positive at assessment AND have symptoms of COVID-19 within the past 1 month.Clinically significant disease refers to those who develop symptoms due to SARS-CoV-2 and require hospitalisation or intensive care unit admission.Re-positivity refers to those who test positive within 90 days of the first RT-PCR results with symptoms.Re-infection refers to those who test positive after 90 days of the first RT-PCR results with or without any symptoms.

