### Key comparisons in the study

We will make comparisons between:

Incidence rates of infection overall and in seropositive and seronegative subgroups.Incidence rates of infection among the vaccinated individuals in the cohorts.Kinetics and longevity of memory B and T cells in infections occurring in the seropositive and seronegative cohort.Baseline cross-reactive T cells and antibodies to non-SARS-CoV-2 β-CoV between symptomatic infections versus asymptomatic infections versus uninfected individuals in the seronegative cohort.Baseline SARS-CoV-2-specific memory T and B cells and antibody levels between infected individuals versus uninfected individuals in the seropositive cohort.

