## Discussion

To our knowledge, this study is the first to follow up a cohort in India, for a period of 2 years for COVID-19 infection and re-infection. In terms of surveillance of SARS-CoV-2 infection, though the nasopharyngeal swab has been the gold standard for diagnosis, the use of saliva samples will be an acceptable alternate by the study participants as it is self-directed, non-invasive and has a good concordance with the nasopharyngeal swab. The study aims to address several gaps in the current scientific evidence of SARS-CoV-2 infection and immunity. First, there are a limited number of studies that investigate the long-term follow-up of individuals for the rates of infection and re-infection in the community. Second, the study aims to look at the kinetics of IgG antibodies following infection. The cross-reactivity between SARS-CoV-2 and other hCoV will support better understanding of determinants of symptomatic infection. The T cell and B cell memory responses would help in understanding the kinetics and longevity of immune responses in seropositive and seronegative individuals and would help in decision-making with regard to booster vaccination. By studying the immunity and the risk of re-infection, we can potentially understand the factors that contribute to symptomatic COVID-19 infections. The study design will also allow the study of how the various VOCs contribute to re-infections. Large-scale vaccination had begun by the time enrolment had been completed. We anticipate that the majority of participants will be vaccinated at the end of the study and would have a hybrid immunity resulting from past infection and vaccine. In view of the 1-year intensive follow-up that requires weekly samples, we have planned to use salivary RT-PCR and only symptomatic individuals will receive nasopharyngeal swab for RT-PCR.

To conclude, CORES will help in estimating the re-infection rates, detailed immunogenicity among the COVID-19-positive individuals, establish the antibody kinetics and characterise the breakthrough infections among the vaccinated individuals in the community.

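### Spike IgG is sufficient for the label of past infection with no condition on vaccination, so participants vaccinated before the baseline draw and never infected can be classed as previously infected

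*Protocol article*

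**What the plan says.** The Abstract states the aim as comparing people without and with "evidence of prior infection as defined by the presence of antibodies to SARS-CoV-2 spike protein". Key definitions then fixes the marker: "Seropositive is defined as serum/plasma samples positive for IgG spike protein antibody to SARS-CoV-2", and "The cut-off for seropositivity is more than or equal to 33.8 BAU/mL". The definition of past infection builds on it: "Past asymptomatic infection refers to those who are seropositive", with a documented positive RT-PCR more than 1 month earlier as the alternative route, provided that the person is test-negative at baseline and has had no symptoms. Past symptomatic infection is built the same way, with past symptoms. Neither definition mentions vaccination. Serological assays names spike IgG and no other antibody test.

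The assumptions under Statistical considerations equate having antibodies at baseline with being exposed, and the sample size is set for a difference between re-infection and primary infection. Key comparisons lists "Incidence rates of infection overall and in seropositive and seronegative subgroups". Key definitions, however, has its own definition of the event: "Re-infection refers to those who test positive after 90 days of the first RT-PCR results with or without any symptoms".

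On vaccination, the Discussion says: "Large-scale vaccination had begun by the time enrolment had been completed". Status is recorded at baseline and checked against certificates (Establishment of the cohort). It is a covariate in the planned model (Statistical analysis).

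**The concern.** Vaccination is expected to raise spike IgG. The documents do not say this, so it is treated here as an assumption with a range. If it does, a participant vaccinated before the baseline draw and never infected is seropositive and, if symptom-free and test-negative, meets the written definition of past asymptomatic infection. Box 1 shows the same asymmetry: under Objective 2, the group without prior infection also excludes vaccinees, while the group with prior infection does not.

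Three results are affected. The infection rate in the seropositive group, read as a re-infection rate, can contain first infections. The four vaccination-by-infection groups cannot be formed as intended for people vaccinated before the draw: the vaccinated-seronegative group nearly empties, and the vaccinated-seropositive group becomes a mixture. The separate hazard ratios promised for vaccination and for previous infection then rest partly on that mixture.

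**Working it through.** **1. The plan's own figure.** From the assumptions section: 50% seropositive, 40% vaccinated, and annual incidence of 12% (unvaccinated seronegative), 6% (vaccinated seronegative), 4.8% (unvaccinated seropositive) and 4% (vaccinated seropositive).

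- Seronegative: 0.6 × 12 + 0.4 × 6 = 9.6%.
- Seropositive: 0.6 × 4.8 + 0.4 × 4 = 4.48%.
- Difference: 5.12 points.

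With 1200 less 10% = 1080, or 540 per group, a two-proportion test with pooled variance (two-sided 0.05 assumed, as alpha is not stated) has 90.9% power. The stated 90% is reproduced. This point does not make the sample size wrong.

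**2. Size of the mislabelling.** Assumptions not in the documents: 50% truly infected; a share v vaccinated before the baseline draw, independently of infection; all vaccinees spike-positive. Rates are the plan's.

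- Seropositive share: 0.5 + 0.5v
- Never infected among seropositives: 0.5v / (0.5 + 0.5v)
- Infections per 100 participants in the truly infected: I = 0.5 × [(1 − v) × 4.8 + v × 4]
- Infections per 100 participants in vaccinated, never-infected seropositives: M = 0.5v × 6
- First infections among all infections in seropositives: M / (I + M)
- Crude rate ratio: [(I + M) / (0.5 + 0.5v)] / 12, since all remaining seronegatives are unvaccinated at baseline

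| v | Never infected among seropositives | I | M | First infections | Seropositive rate | Crude RR |
|---|---|---|---|---|---|---|
| 0% | 0% | 2.40 | 0 | 0% | 4.80% | 0.40 |
| 20% | 0.10/0.60 = 17% | 2.32 | 0.60 | 0.60/2.92 = 21% | 4.87% | 0.41 |
| 40% | 0.20/0.70 = 29% | 2.24 | 1.20 | 1.20/3.44 = 35% | 4.91% | 0.41 |
| 60% | 0.30/0.80 = 38% | 2.16 | 1.80 | 1.80/3.96 = 45% | 4.95% | 0.41 |

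Over a wider range (30–50% truly infected, 10–40% vaccinated before the draw, 80–100% spike-positive after vaccination), 7–48% of seropositives would be never infected, and 9–56% of their infections would be first infections.

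**3. Vaccine effect among seropositives.** Under the assumptions of step 2, half of the vaccinated seropositives are truly infected, so their rate is 0.5 × 4 + 0.5 × 6 = 5.0%. Against 4.8% in unvaccinated seropositives the ratio is 5.0/4.8 = 1.04, where the plan's own rates give 4/4.8 = 0.83. The result does not depend on v. With 30–50% infected and 80–100% spike response it runs from 1.02 to 1.13.

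**4. The two meanings of re-infection.** By the aim and the sample size section, an infection in a seropositive participant is a re-infection. By Key definitions, it is one only if more than 90 days have passed since that person's first RT-PCR result. A vaccinated seropositive participant with a first-ever positive RT-PCR during the study is in the re-infection group by the former and not a re-infection by the latter.

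**The case against.** **Spike IgG is not the only route.** A documented RT-PCR also qualifies. This is correct, but that route adds people to the past-infection group and removes no vaccinee.

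**First infections are not re-infections under the written definition.** This stands as far as Key definitions goes. The consequence follows only from the aim and the sample size section, which is why the point here is a conflict to be reconciled.

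**Vaccination is recorded and adjusted for, and an unvaccinated contrast can be formed from the planned groups.** Both are true, and they make the fix cheap. But adjustment does not show which vaccinated seropositives had been infected, and the ratio of 1.04 in step 3 already comes from comparing within serostatus.

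**Coverage at the draw is unknown.** This stands. The plan's 40% refers to two doses mid-way into the study. For anyone vaccinated after the draw, the baseline result is unaffected by vaccination.

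**A reader might infer that protection from natural infection is overstated.** At v = 40%, the crude ratio of 0.41 is indeed below 4.48/9.6 = 0.47. But 0.47 averages over vaccination status. Against the unvaccinated contrast, 4.8/12 = 0.40, the crude ratio differs by about 0.01 and lies towards the null. The documents do not support a claim of inflated protection.

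**Conclusion.** The definition needs correcting as written. It makes spike IgG sufficient for past infection, sets no condition on vaccination and names no infection-specific serology, although vaccination was under way before enrolment closed. What suffers is the meaning of the infection rate in seropositives, where roughly a fifth to nearly a half of the events could be first infections at 20–60% coverage before the draw. The vaccine effect among seropositives suffers too and could appear as 1.04 instead of 0.83. Both results rest on the assumed infected share and spike response, and the first also on coverage at the draw. If nobody was vaccinated before the draw, there is no mislabelling from this source. The reproduced power and the crude rate ratio are not the problem.

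**What to change.** Using the certificate-verified vaccination dates:

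1. Let spike seropositivity count as prior infection only when the blood was drawn before any vaccine dose, or less than 14 days after dose 1.
2. Among participants already vaccinated at the draw, call previously infected only those with a documented earlier positive RT-PCR or antigen test. Report the rest as a separate group: vaccinated, infection status unknown.
3. Report seropositive versus seronegative among those unvaccinated at the draw as the estimate of protection from natural infection, alongside the planned adjusted model.
4. Reconcile the two meanings of re-infection, so that the event in the aim, the sample size section and Key definitions is the same.

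This changes wording and derivations and needs no new visits. The cost is a smaller contrast. With 1080 evaluable and half of the unvaccinated seropositive, each group has 1080 × (1 − v) / 2 participants. For 12% versus 4.8% (two-sided 0.05 assumed), power is 97% with 432 per group (v = 20%), 91% with 324 (v = 40%) and 77% with 216 (v = 60%), before any loss from vaccination during follow-up.

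Anti-nucleocapsid testing of stored baseline samples, for recipients of spike-only vaccines, is an optional addition with reagent costs and is not part of the required change.

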#### Intensive follow-up phase

The first year following recruitment of the cohort would be the intensive follow-up phase during which weekly follow-up visits and saliva sampling are planned. An assigned field research assistant (FRA) will contact the study participant every week, either by telephonic or direct visit, and collect information regarding any COVID-19-like symptoms in the preceding week. The study participants will be trained to collect 2 ml of saliva in the universal sample container, early in the morning, on one designated day of the week. The participants will be asked to collect these samples as per the study protocol, prior to routine oral hygiene, and consumption of any food or drink. The samples will be collected by the FRAs and transported to the laboratory in vaccine carriers with ice packs to maintain a temperature of 4°C. The samples, once received in the laboratory, will be aliquoted in two vials. One vial will be retained at the Wellcome Trust Research Laboratory, Vellore. The other vial is sent to the National Centre for Biological Sciences, Bangalore (NCBS) for RT-PCR.

If an individual tests positive for SARS-CoV-2, the weekly salivary sample collection will be suspended for the next 90 days. The weekly contact, however, will be continued. During the weekly contact, if a subject develops symptoms, their samples will be collected. If they are RT-PCR positive within 90 days, it will be considered as re-positive. The study participants will be requested to inform the study team if they experience any clinically significant febrile or respiratory distress. Symptomatic individuals will be advised to visit CMC Hospital, Vellore and get tested by nasopharyngeal RT-PCR, as deemed necessary, after clinical examination. Clinical symptoms, response to treatment and details of treatment during hospitalisation or during home management would be recorded on the case report form (CRF) for every participant who is positive by RT-PCR.

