#### Follow-up phase: second year

During the second year of the study, weekly follow-up would be through telephonic interviews. Weekly salivary samples will not be collected, and home visits will be done only for subjects with symptoms. Any incident infection will be followed up for detailed immunological testing. Once every 6 months, a blood sample (5 mL) will be collected for assessing the serostatus of the participants to identify any infection that was missed through the RT-PCR screening. Sequencing will be done on all positive samples to identify the genetic sequence of the virus at NCBS, Bangalore and help us determine which VOC was responsible for the infections and re-infections. This will include samples classified as ‘re-positives’.

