### Laboratory procedures

#### Weekly salivary samples

Upon receipt and aliquoting, salivary samples will be pooled for testing on the same day. Ten microlitres of five samples each will be pooled in a single well of the PCR plate, and 6 µL of proteinase K of 50 µg/µL concentration will be added to each well. Subsequently, the plates will be sealed and heated at 95°C for 5 min in a dry thermal bath. After heat inactivation, the plates will be stored at −80°C. The pooled PCR plate and an aliquot of saliva will be transported on dry ice to NCBS. RT-PCR will be performed on the pooled samples targeting the N gene, E gene and RdRp gene of SARS-CoV-2. The limit of detection of the commercial kit that is used for testing is 100 copies/mL and the sensitivity of detection in saliva samples is around 94% compared with nasopharyngeal swab.^19^ If any pool turns out to be positive, RT-PCR will be performed on individual samples. All positive samples will undergo sequencing.

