### Statistical analysis

Seroprevalence is estimated as a proportion and will be assumed to follow a binomial distribution. The incidence of infection within the cohort is expected to follow a Poisson distribution. We will permit repeated infections to be captured in analysis and account for the same in the analysis. A time-to-event analysis using Prentice, Williams and Peterson models comparing incidence in the exposed and unexposed cohorts will be performed. We will adjust for background infection rates in each cluster (ward) and covariates such as age, socioeconomic status, vaccination status, per-capita floor space and occupation class.

The statistical analysis plan will detail the estimation of seroprevalence, its risk factors, the incidence of primary and re-infection, and a comparison of these rates. Continuous variables will be described using mean (SD) and median (IQR) where necessary. Categorical data will be expressed as frequency (%). Incidence of infection and re-infection will be calculated per thousand person-years. HRs will be estimated to assess protection/risk conferred by vaccination and previous infection.

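### Re-infection is defined by the 90-day interval alone, so residual RNA could be counted among the few in-study second events although all positives are sequenced

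*Protocol article*

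**What the plan says.** Key definitions, in the protocol article, sets the rule: "Re-infection refers to those who test positive after 90 days of the first RT-PCR results with or without any symptoms". No intervening negative, symptom or difference in sequence is required.

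Under Intensive follow-up phase, after a positive test "the weekly salivary sample collection will be suspended for the next 90 days". Weekly contact continues, and only participants who develop symptoms are sampled in that window. For those, "If they are RT-PCR positive within 90 days, it will be considered as re-positive". Weekly saliva belongs to year 1 only: "The first year following recruitment of the cohort would be the intensive follow-up phase". In year 2, detection depends on symptoms, with six-monthly serology.

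On sequencing, Follow-up phase: second year says "Sequencing will be done on all positive samples to identify the genetic sequence of the virus", re-positives included, and the laboratory section repeats it: "All positive samples will undergo sequencing". The stated purpose is to "help us determine which VOC was responsible for the infections and re-infections". Nothing in the text uses the sequence to decide whether a late positive is a re-infection.

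Statistical analysis then takes repeat events into Prentice, Williams and Peterson models: "We will permit repeated infections to be captured in analysis".

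**The concern.** RT-PCR detects RNA. By itself it cannot tell a new infection from RNA left over from the previous one. The plan accepts this inside 90 days, where it has a separate re-positive class, but beyond day 90 the calendar alone decides. Because routine sampling is suspended, the first resumed saliva sample of a participant without symptoms usually has no negative before it. If that sample is positive it becomes a second event, even if its sequence matches the first episode.

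This error can only add events. It would raise the in-study re-infection rate and the second-event stratum of the recurrent-event model. It would also credit the first episode's variant with a re-infection. Blood draws could be mislabelled too: the day 90 (+7 days) sample of the first episode falls just when weekly saliva resumes, so a draw at about that time could be recorded as day 0 of a new infection. Since few true second events are expected, one or two false ones would show.

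**Working it through.** **Inputs from Statistical considerations.** 1200 participants, 10% dropout, 50% seropositive, 40% vaccinated. Annual incidence is 12% and 6% (seronegative, unvaccinated and vaccinated) and 4.8% and 4% (seropositive, likewise).

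**The plan's own figure first.**
- Seronegative: 0.6 × 12% + 0.4 × 6% = 9.6%.
- Seropositive: 0.6 × 4.8% + 0.4 × 4% = 4.48%. The difference is 5.12 points.
- Two proportions, pooled variance, two-sided 0.05 (assumed, as alpha is not stated), 90% power: 523 per group, and 1046/0.9 gives 1163. With a difference of exactly 5 points (9.6% against 4.6%): 553 per group, 1229 in total.
- Both are close to 1200, and 540 per group gives 90.9% power for 9.6% against 4.48%. The blended rates therefore fit the plan.

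**First infections in year 1.** 540 × (0.096 + 0.0448) = 51.8 + 24.2 = 76.

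**Time at risk of a countable second event** (first infections assumed uniform over 365 days):
- Resuming weekly saliva within year 1: 76 × 275/365 = 57.3 people.
- Mean time from day 90 to the end of year 1: 275²/(2 × 365) = 103.6 days = 0.284 years. Total 76 × 0.284 = 21.6 person-years.
- Mean time from day 90 to month 24: 730 − 182.5 − 90 = 457.5 days = 1.253 years. Total 76 × 1.253 = 95.3 person-years.

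**True second events**, taking the repeat rate as the seropositive rates:
- Year 1: 21.6 × 4% to 4.8% = 0.86 to 1.04 (0.97 at 4.48%).
- To month 24, all detected: 95.3 × 4% to 4.8% = 3.8 to 4.6 (4.27 at 4.48%).
- To month 24, half of year-2 events detected (assumption): 0.97 + 3.30/2 = 2.62 at 4.48%.

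**False second events.** 57.3 × p, where p is the fraction still RNA-positive when saliva resumes. The documents give no value, so p is an assumed range that includes zero. The share is false/(false + true), at 4.48%:

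| p | False events | Share, year 1 | Share, 24 months, all detected | Share, 24 months, half of year 2 detected |
|---|---|---|---|---|
| 0% | 0 | 0% | 0% | 0% |
| 0.5% | 0.29 | 23% | 6% | 10% |
| 1% | 0.57 | 37% | 12% | 18% |
| 2% | 1.15 | 54% | 21% | 30% |
| 3% | 1.72 | 64% | 29% | 40% |

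At p = 3%, repeat rates of 4.8% and 4% give 62% and 67% for year 1, and 27% and 31% for 24 months with all detected.

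**Sensitivity to the repeat rate r.** The year-1 share is p/(p + 0.377r), because 21.6/57.3 = 0.377. It depends on p and r, not on cohort size. At r = 12%, true year-1 events are 2.6, and the share at 1%, 2% and 3% falls to 18%, 31% and 40%.

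**Effect on the powered contrast.** If p is the same in both serostatus groups, false events add 0.753 × p to each group's infections, at most 2.3% at p = 3%. The ratio between groups does not move. If all 1.72 false events fell among the 24.2 infections in baseline seropositives, that total would rise by 7%.

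**The case against.** The strongest reply is that the bias is assumed rather than shown. The documents contain no persistence figure, and zero is possible. Several features point to the low end: immunocompromised people are excluded, saliva is tested in pools of five so weak RNA must first turn a pool positive, and the 90-day interval is itself a guard against residual RNA. All of this stands, and it is why the range starts at zero.

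A second reply is that the year-1 share uses the least favourable denominator, since follow-up lasts 24 months. That also stands, so both shares are given.

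Third, the abstract describes re-infection as infection in people with antibodies, and the sample size rests on the contrast between re-infection and primary infection. A reader might infer that this comparison is biased, or that most reported re-infections will be artefact. The documents support neither. The serostatus contrast rests mainly on first in-study infections, and the larger shares need both p near 3% and a count limited to year 1.

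Fourth, the article leaves detailed estimation to the statistical analysis plan, and the unseen Figure 1 has a legend naming sequencing and cycle threshold. Either could hold a grading step. But the event definition is stated in the text, and as stated it is complete without one.

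Finally, sequences will not settle every case. Low-RNA samples may fail, a swab taken at another institution may not be available for sequencing, and one negative saliva followed by a matching positive fits intermittent shedding. These limits shape the fix but do not remove the need for it.

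**Conclusion.** The point holds in a limited form. The stated definition counts any positive after 90 days as a new infection, the sampling pause normally removes the chance of a clearing negative, and the planned sequences are given no role in classification. The exposure is confined to in-study second events: about 1 true event in the weekly-PCR year and 3.8 to 4.6 over 24 months. At an assumed persistence of 0% to 3%, 0 to 1.7 false events are added. That is 0% to about 65% of the year-1 count and 0% to about 31% of the 24-month count if all true events are found, or up to about 40% if only half of year-2 events are.

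These figures rest on the plan's attack rates, uniform timing of first infections, a repeat rate equal to the seropositive rates, and the assumed persistence. They show a possible bias of uncertain size, not a demonstrated one. The powered comparison is little affected.

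**What to change.** Keep the rule of more than 90 days for the main count, and grade every late positive with data already planned:

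- **Sequence-confirmed:** lineage or genome distinct from the first episode.
- **Probable:** intervening negative saliva samples, but no usable pair of sequences.
- **Possible persistence:** sequence matches the first episode, above all with no intervening negative. A negative saliva in between does not by itself move a matching sequence out of this grade.
- **Unclassified:** neither can be assessed.

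State what counts as distinct before the pairs are compared. Report the re-infection rate and the recurrent-event model three times: as defined, with possible-persistence events excluded, and with sequence-confirmed events only. If there are too few second events to fit the model, give counts and rates by grade.

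The cost is one added definition and two repeat analyses, with no new samples. There is a downside to state openly: some true re-infections with the same circulating lineage will be graded as possible persistence, and low-RNA samples may fail sequencing. The results should therefore be presented as a range, with no single count treated as the correct one.
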